**Methods:**

In the prospective randomized controlled trial, 160 participants will be recruited and randomized to the treatment group (BDJ exercise combined with Calcium carbonate and D3) or the control group (Calcium carbonate and D3) at 1:1 ratio. Participants in the treatment group will receive 24-week BDJ exercise for 30–60 min, 3 times a week, along with Calcium carbonate and D3 at each day, while participants in the control group will receive Calcium carbonate and D3 only. All outcome indicators will be measured at baseline, after the 6th month of treatment and 6th month after the end of treatment. The primary outcomes include pain and balance ability, as measured by the visual analogue scale (VAS) and Berg balance scale (BBS). The secondary outcomes will primarily include bone mineral density (BMD), laboratory tests (including P1NP, β-CTX, MSTN, FDF-23, NPY), the timed “up and go” (TUG) test, the morse fall scale (MFS), the five-times sit-to-stand test (FTSST).

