Bone mineral density (BMD) is the gold standard for OP, however, one of the characteristics of OP is pain and the serious outcome is fracture, and then, balance ability is closely related to the occurrence of fracture [9]. Therefore, the study focused on pain and balance ability, two key factors associated with the development of OP. At first, we conducted a systematic review and meta-analysis in order to initially explore the therapeutic effect of BDJ exercise on OP [17], and the results suggested that it might be beneficial to improve BMD, relieve pain, improve balance ability, influence serum bone gla protein (BGP) and alkaline phosphatase (ALP) in patients with OP, and we also found previous studies to be of low quality. Therefore, we will plan to conduct a prospective superior randomized controlled trial and further determine the effectiveness of BDJ exercise on pain and balance improvement, which can provide a broad perspective in relationship between BDJ and OP.

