### Intervention

During the trial period, participants in the treatment group will be given BDJ exercise combined with Calcium carbonate and D3, and in the control group will be only given Calcium carbonate and D3. The intervention period will last 24 weeks. The requirements for the BDJ exercise will be as follows.Preparatory stage (the first 2 weeks, mastering movements stage)Participants need to be organized to practice BDJ exercise for 3 times a week. The researchers will hire professional coaches to guide and correct the movements. During rest time, research assistants will distribute free videos to practice by themselves at home.Conventional stage (the last 22 weeks, regular exercise stage)The participants need to exercise 3 times a week, 30 to 60 min each time, and the amount of exercise may be appropriate as long as the participants do not experience fatigue. The research assistants will lead exercise once a month, and the rest time will be practiced by themselves. The researchers will give monthly follow-up calls or home visits to record the completion and adjust the exercise frequency according to the actual conditions. During the trial period, the researchers will instruct the participants to avoid other physical activities as much as possible, for example, swimming. If there are associated exercises, the research assistant needs to record details.We will recommend the participants form a small team to exercise together with their familiar people, and distribute free brochures, BDJ exercise teaching videos and special lectures about OP at different periods, so as to maximize enthusiasm and compliance, which can ensure the study completion to the greatest extent.

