### Outcome assessment

Variables in this study included basic information, clinical characteristics, adverse events, primary and secondary outcomes. We will collect basic information and clinical characteristics at baseline (1 week before randomization). Primary and secondary outcomes will be measured at baseline and after the 6th month of treatment (6 months after enrollment). In addition, follow-up assessments will be conducted at 6th month after the end of treatment (12 months after enrollment). All primary and secondary outcomes will be assessed by professionally qualified doctors who will be unaware of assigned outcomes.Basic information and clinical characteristicsResearch assistants will use the Case Report Form (CRF) designed for this study to collect basic information and clinical characteristics, including gender, age, education, height, weight, waist circumference, hip circumference, co-morbid history, personal life history and medication use. Body mass index (BMI) was calculated from height and body mass, and waist-to-hip ratio was calculated from waist circumference and hip circumference.Primary outcomesPain induced OP is measured using the visual analogue scale (VAS, 0–10 points). 0 point represents no pain, 1–3 points are mild pain, 4–6 points represent moderate pain, although the pain is strong but still tolerable, 7–10 points represent severe pain, which gradually reaches difficult degree of tolerance.Balance ability is measured using the Berg balance scale (BBS, 0–56 points). The higher the score, the better the balance ability. At the same time, the risk of falling can be assessed according to the results: BBS < 40 points means at risk of falling.Secondary outcomesBone mineral density (BMD) is measured using DXA. Fixed professionals are responsible for the verification and measurement of the machine, and the inspection parts mainly include lumbar vertebrae (L1-L4) and bilateral hips.Laboratory tests (blood serum) are measured with Luminex Assay. With reference to the Recommended Experiments for Biochemical Indicators of Bone Metabolism (2020 Expert Consensus, China) [20], the preliminary research results, and the literature survey, The serological indicators include Type I Procollagen N-terminal Propeptide (P1NP), β-collagen Degradation Product (β-CTX), Myostatin (MSTN), Fibroblast Growth Factor-23 (FGF-23), and Neuropeptide Y (NPY). Qualified researchers will draw 5 ml of venous blood from the participants in the morning on an empty stomach, and complete the aliquots within 30 min.Fall risk is measured with the timed “up and go” (TUG) test and morse fall scale (MFS). Research assistants need to record the time, the participant's gait, and the falling risk according to the following criteria: 1 point is normal, 2 points are very slightly abnormal, 3 points are mildly abnormal, 4 points are moderate abnormality, 5 points are severe abnormality. The MFS was developed by [name] in 1989. The content of the scale evaluation involves the history of falls in the past 3 months, gait, cognition, etc. The total score is 125 points, and the higher the score, the greater the risk of falling. A score greater than 45 is considered high risk of falling, 25 to 45 is considered medium risk, and less than 25 is considered low risk.Lower extremity muscle strength is measured with five-times sit-to-stand test (FTSST). The assistants need to record the total time spent. At last, the test was performed 3 times and the final average was taken.

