### Statistical analysis

All statistical analyses were performed using SPSS 25.0 and Python 3.11. Statistical significance was set at a P value less than 0.05. Continuous variables that conform to a normal distribution are represented by the mean and standard deviation, and variables that do not conform to a normal distribution are represented by the median and interquartile range. Categorical variables will be described as frequencies or percentages. Missing data will be filled in using multiple imputation.

To account for correlation among repeated measurements, intervention effects on the primary and secondary outcomes were examined by generalized estimating equations (GEE) with baseline measurement as the covariates. The group-by-time interaction, which indicated the difference for a given outcome between interventions over time, was considered our primary measure of intervention effects.

Adverse effects will be analyzed using the χ^2^ test or Fisher's test. If it cannot run a normal analysis, we will choose descriptive analysis for presentation.

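### With baseline as a covariate, the group-by-time interaction named as the primary effect measure captures change in the effect after training stops, not the effect of Baduanjin itself

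*Protocol article*

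**What the plan says.** The protocol article settles the relevant points in three places.

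- **Aim.** The Background says the investigators will "conduct a prospective superior randomized controlled trial and further determine the effectiveness of BDJ exercise on pain and balance improvement". This is a superiority question about whether the exercise works.
- **Visits.** Under Outcome assessment, the primary and secondary outcomes are taken at baseline and at 6 months, and "follow-up assessments will be conducted at 6th month after the end of treatment (12 months after enrollment". Under Intervention, "The intervention period will last 24 weeks", so month 6 is the end of treatment and month 12 is about half a year after supervised training ends.
- **Model and primary measure.** Under Statistical analysis, effects on primary and secondary outcomes "were examined by generalized estimating equations (GEE) with baseline measurement as the covariates". The next sentence reads: "The group-by-time interaction, which indicated the difference for a given outcome between interventions over time, was considered our primary measure of intervention effects".

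The article does not say that baseline is also a response in the GEE. It gives baseline one role, that of covariate.

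**The concern.** Once baseline is on the covariate side, two outcome visits remain, and a group-by-time interaction across two visits compares the treatment effect at one with the treatment effect at the other. That is a question about durability. The question in the Background, whether Baduanjin reduces pain and improves balance, is answered by a group difference.

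The consequence on this reading is perverse. A large benefit held unchanged to month 12 gives a null primary result, while a benefit lost after training stops gives the strongest one. The 90% power claimed in the Sample size section would then not describe the test named as primary.

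**Working it through.** **1. The plan's own figure.** 128 / (1 − 0.20) = 160, as stated under Sample size. This reproduces the dropout step only. The 64 per arm cannot be rebuilt, because the article gives no difference or SD.

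**2. What the interaction is.** Let d6 and d12 be the Baduanjin-minus-control differences at 6 and 12 months. With outcome rows at 6 and 12 months and terms for group, visit, group-by-visit and baseline:

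- group coefficient (reference visit month 6) = d6
- group-by-visit coefficient = d12 − d6

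If d12 = d6, the interaction is exactly zero whatever the size of d6. This is algebra and needs no assumption about the data.

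**3. Assumptions for size.**

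- From the article: 64 evaluable per arm, alpha 0.05, power 90%.
- Assumed: a two-sided test (the article does not say), unit SD at each visit, and equal correlation r between visits of 0.3, 0.5 or 0.7.
- Implied effect: (1.960 + 1.282) × √(2/64) = 3.242 × 0.1768 = 0.573 SD by the normal approximation, or 0.577 SD with the t distribution. The power figures below agree for either value to the precision shown.

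**4. Formulas.** Standard error = SD × √(2/64), with

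- interaction: SD of the 6-to-12-month change = √(2(1 − r)) = 1.183 / 1.000 / 0.775
- baseline-adjusted 6-month contrast: residual SD = √(1 − r²) = 0.954 / 0.866 / 0.714

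Example at r = 0.5 with half retained: interaction 0.577 × 0.5 = 0.289, SE 0.177, ratio 1.63, power 37%. For the 6-month contrast: 0.577 / 0.153 = 3.77, power 96%.

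**5. Power, outcome rows at 6 and 12 months.**

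| Share of 6-month effect kept at 12 months | Interaction, r = 0.3 / 0.5 / 0.7 | Adjusted 6-month contrast |
|---|---|---|
| 100% | 5% / 5% / 5% | 92.5% / 96% / 99.5% |
| 75% | 11% / 13% / 18% | same |
| 50% | 28% / 37% / 55% | same |
| 25% | 54% / 68% / 88% | same |
| 0% | 78% / 90% / 99% | same |

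**6. Check with fitted GEEs** (300 simulated trials, 64 per arm, r = 0.5, sustained benefit of 0.573 SD, with benefit coded as negative). The interaction averaged −0.01 and was rejected in 7%, which is the nominal 5% within simulation error. The 6-month group difference from the same model averaged −0.57 SD and was rejected in 94%. The group effect averaged over both visits (model without the interaction) was also −0.57 SD and was rejected in 99%.

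**7. The other reading: baseline also kept as an outcome row.** The month-6 interaction is now the difference between groups in change from baseline, so it does estimate the treatment effect. In the same simulation it averaged −0.57 SD with 87% rejection, and the figures were the same whether or not baseline was added as a covariate. The reason is that a person's baseline value is constant over visits. With complete or imputed data and a separate mean for each group at each visit, it cancels from every group-by-visit term. The SD is again √(2(1 − r)), so 6-month power is 78% / 90% / 99%, against 92.5% / 96% / 99.5% for the adjusted contrast.

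**The case against.** The strongest reply is that the text never excludes baseline from the response. It speaks of repeated measurements, outcomes are recorded at three visits, and its gloss on the interaction is close to how a group-by-visit term measured against baseline is usually described. On that reading a sustained benefit appears in full at month 6. A joint two-degree-of-freedom interaction test at r = 0.5 would have about 93% power if the benefit is sustained, 84% if half is retained and 93% if it is lost. The perverse behaviour is gone.

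This stands as a limit on the point. A reader might infer that the trial is bound to call a lasting benefit ineffective, or that the planned beta of 0.10 cannot apply to the primary test. The document supports neither without the condition that only the 6- and 12-month values are outcomes. With baseline as an outcome row, the 6-month term has about 90% power at r = 0.5.

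The reply does not clear the sentence. It needs a role for baseline that the article does not state, and it leaves the role that is stated without effect on the primary term.

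A reader might also count the lack of a named primary visit as a defect in itself. A condensed article commonly leaves that to the full protocol or SAP, so it is not part of this point. The objection is to the effect measure the article does name.

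**Conclusion.** The concern holds in conditional form. On the plain reading, the stated primary measure answers whether the effect changes after training stops. It has only the 5% false-positive rate when the benefit is fully sustained, whatever the correlation, and the stated 90% power does not describe it. On the alternative reading the measure is valid, the stated baseline adjustment is empty, and the cost is precision: about 14 percentage points of power at r = 0.3, 6 at r = 0.5 and under 1 at r = 0.7. Neither reading makes the two sentences work together as written.

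The zero under a sustained benefit is exact. The power figures are illustrations: they rest on an effect back-calculated from 64 per arm, a two-sided test, equal correlations and complete data, none of which the article supplies. They show the direction and rough size of the problem and are not a forecast for this trial.

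**What to change.** Before unblinding, replace the sentence that makes the interaction primary. Suggested wording: *The primary measure of the intervention effect is the baseline-adjusted Baduanjin-minus-control difference, estimated from a GEE on the 6- and 12-month values with terms for group, visit, group-by-visit and baseline value, at [the named visit, or averaged over both visits].*

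The sponsor should choose and state the contrast. Month 6, the end of treatment, is one natural choice, and the average over both visits is another; the document does not dictate either. If one visit is primary, report the other as secondary. Report the interaction only as a description of how the effect changes. Baseline should not serve as both outcome row and covariate.

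The cost is rewording: the same model family, the same data, and no extra visits or patients.

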### Randomization

Participants who meet the inclusion and exclusion criteria will be randomly divided into the control group and the treatment group, with 80 patients in each group. Due to the peculiarities of BDJ exercise itself, we could not blind participants or trainers, but outcome assessors and statisticians will be blind. The research will entrust a professional data management department to generate random numbers system (http://112.126.58.121:8082/bdj) and monitor trial quality. According to the group designated by the random number, research assistants accurately record the participants' random number, group, and intervention.

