
### Safety measurements

Research assistants will monitor participants for adverse events during the treatment. Research assistants guide the preparation and relaxation exercises before and after the practice to prevent the elderly from being injured. During the trial period, the BDJ exercise should be stopped if serious complications, other diseases, or adverse reactions occur. Meanwhile, corresponding treatment measures should be taken. Any adverse events that occur will be reported immediately and in detail to the research center that will assess the causal relationship and severity associated with the intervention. Serious adverse events will be reported to the ethics committee to decide the next steps.

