### Sample size

According to the existing results combined with expert experience [21, 22], we assume α = 0.05 and β = 0.10 based on an allocation ratio of 1:1, then the sample size is 64 cases respectively in the two groups, totaling 128 cases according to VAS. Considering the 20% dropout rate, a total sample size of 160 cases is required. Then, we also calculated the sample size to be 146 cases according to BBS. Finally, we set the sample size of this study to 160 cases.

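### Harms are compared between arms only by a chi-square or Fisher P value, which at 80 per arm says little about uncommon harms; add counts and risk differences with confidence intervals (minor)

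*Protocol article*

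**What the plan says.** The between-arm analysis of harms is given in two sentences under Statistical analysis. The first reads "Adverse effects will be analyzed using the χ^2^ test" and offers Fisher's test as the alternative. The second gives the fallback: "If it cannot run a normal analysis, we will choose descriptive analysis for presentation". No rule is given for choosing between the two tests. The same section sets the threshold for all analyses: "Statistical significance was set at a P value less than 0.05". It also says, for categorical variables generally, that frequencies or percentages will be given.

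Under Safety measurements, any adverse event "will be reported immediately and in detail to the research center that will assess the causal relationship and severity associated with the intervention", and serious events go to the ethics committee. The article does not say whether those who assess causality are blinded. Outcome assessment lists adverse events as a study variable, separately from the primary and secondary outcomes whose assessors are blinded. The term therefore changes between sections: adverse events are collected, but adverse effects are tested.

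Randomization fixes the arm size, "with 80 patients in each group". The Sample size section derives the total from VAS and checks it against BBS; harms play no part in it.

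**The concern.** A significance test answers a narrow question about harms, and a trial of this size answers it poorly when events are few. A large P value is then compatible both with no excess and with an excess that would matter in people with low bone density. The P value alone does not show which, whereas an interval does.

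Two features of the stated plan add to this:

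- **Choice of test.** Two tests are named without a rule for choosing, and on sparse tables they can fall on opposite sides of 0.05.
- **Quantity tested.** The word *effects* leaves open whether all events or only those attributed to the exercise are compared. Control participants do no Baduanjin under the protocol, so they cannot contribute exercise-related events, and a test on those events would not be a like-for-like comparison.

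At stake is how the harms result is read beside the efficacy result. The authors hope that the trial will support recommending the exercise in osteoporosis, so the harms summary should show how large an excess the data leave open.

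**Working it through.** **Inputs from the article.** Threshold P < 0.05 (Statistical analysis; sidedness not stated, two-sided taken here). Arm size 80 (Randomization). 64 per group on VAS and 20% dropout (Sample size).

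**The plan's own figure.** 128 / (1 − 0.20) = 160, or 80 per arm, as stated. The 64 per group cannot be re-derived because the article gives no difference or standard deviation. No event rate or power for harms is given.

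**The two named tests on one sparse table, 5/80 v 0/80.**

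- Smallest expected count: (5 + 0) / 2 = 2.5.
- Fisher, two-sided: 2 × C(80,5) / C(160,5) = 2 × 0.0293 = 0.0586.
- Uncorrected chi-square: 160 × (5 × 80 − 75 × 0)² / (80 × 80 × 5 × 155) = 25,600,000 / 4,960,000 = 5.16 on 1 df, P = 0.023.
- Chi-square with Yates correction: P = 0.069.

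Neighbouring tables at 80 per arm:

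| Events | Fisher P | Uncorrected chi-square P | Yates P |
|---|---|---|---|
| 4 v 0 | 0.120 | 0.043 | 0.129 |
| 5 v 0 | 0.059 | 0.023 | 0.069 |
| 6 v 0 | 0.028 | 0.013 | 0.037 |
| 7 v 1 | 0.064 | 0.030 | 0.070 |
| 8 v 1 | 0.034 | 0.016 | 0.040 |

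At 4 v 0, 5 v 0 and 7 v 1 the verdict at 0.05 depends on which test is run. With 64 per arm the 5 v 0 results are almost the same: Fisher 0.058, uncorrected chi-square 0.0225, Yates 0.068.

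**Power at 80 per arm.** Power is the sum, over all tables with P < 0.05, of Bin(a; 80, p1) × Bin(b; 80, p2). The rates are assumptions, chosen to span uncommon to moderately common harms. The last column uses Fisher when the smallest expected count is below 5 and uncorrected chi-square otherwise, which is the usual convention.

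| Assumed true rates | Fisher | Uncorrected chi-square | Usual convention |
|---|---|---|---|
| 2% v 6% | 11% | 22% | 12% |
| 2% v 10% | 44% | 57% | 49% |
| 5% v 15% | 48% | 57% | 57% |

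Whichever test is used, power stays below 60% in these scenarios, against the 90% planned for VAS ("we assume α = 0.05 and β = 0.10 based on an allocation ratio of 1:1").

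**What an interval adds.** For 5/80 v 0/80 the risk difference is 5/80 − 0 = 6.25 points. The Wilson limits are 2.70% to 13.81% for 5/80, and 0 to 4.58% for 0/80. The Newcombe limits are:

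- lower: 6.25 − √[(6.25 − 2.70)² + 4.58²] = 0.5 points (0.45 before rounding)
- upper: 6.25 + (13.81 − 6.25) = 13.8 points

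The reader sees an excess that could be small or could approach 14 points. That is more useful than a P value of 0.023 or 0.059, depending on the test.

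**The case against.** The strongest reply is that chi-square or Fisher tests for adverse events are conventional, low power for rare harms affects almost every trial of this size, and naming a test does not exclude an interval. The general sentence on frequencies or percentages would cover adverse-event counts, and the Safety measurements section adds case-by-case review of causality and severity. Much reporting detail also belongs in a full protocol or analysis plan that is not shown. This largely stands, and it limits the point to a minor one. What survives is that the stated between-arm method is a P value, percentages and case review give no between-arm estimate with its uncertainty, and the two named tests can disagree on the same counts.

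The documents do not support four stronger readings that a reader might infer:

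- **Both tests miss 5 injuries against 0.** Fisher and the Yates-corrected chi-square do. The uncorrected chi-square does not, and it is significant even at 4 v 0. Fisher thresholds such as 10 v 2 or 13 v 4 should not be quoted as the plan's thresholds either: the smallest expected counts there are 6 and 8.5, where chi-square is the usual choice.
- **A non-significant result will be declared safe.** The article states no safety hypothesis and no rule for reading P > 0.05. Its aim is effectiveness on pain and balance. The Background calls the exercise safe as a description from earlier literature, and the hoped-for recommendation is not tied to the adverse-event test.
- **Causality is judged by an unblinded centre.** The assessor's blinding status is not given. One can say only that the assessment is not stated to be blinded.
- **Only events attributed to the exercise will be compared.** Nothing says so, and the wording may simply be loose. The ambiguity justifies changing one word; it does not establish a biased comparison.

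**Conclusion.** The point holds as a minor, cost-free improvement and not as a demonstrated error. As stated, the between-arm harms analysis is a P value with low power for uncommon harms: 11% to 48% by Fisher and 22% to 57% by uncorrected chi-square over the assumed rates. With few events, the choice between the two named tests can decide significance (5 v 0: P = 0.059 or 0.023). The power figures rest on those assumed rates, on 80 analysed per arm and on two-sided testing. A one-sided Fisher test would give P = 0.029 at 5 v 0. That a non-significant result may be misread as no harm is a caution about interpretation, not something the article plans.

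**What to change.** In the Statistical analysis section, replace the two sentences on adverse effects with wording to this effect:

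- Report the number and percentage of participants with at least one adverse event, and with at least one serious adverse event, by randomised arm and whatever the attributed cause.
- Give each risk difference with a 95% confidence interval by a method suited to small counts, such as Newcombe.
- If a P value is kept, state the rule for choosing the test, and state that P > 0.05 will not be taken as evidence of no harm.
- Use the term adverse events, as in Outcome assessment and Safety measurements.
- List events judged related to the exercise in a separate descriptive table, since the control arm cannot contribute to it and the causality assessment is not stated to be blinded.

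This costs a few sentences. It needs no new data and no change to sample size or trial conduct.
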